#### Main analysis

Odds ratios, risk differences, and 95 % confidence intervals will be used to compare the primary and secondary outcomes between the two trial groups. A generalised estimating equation model-based analysis will be used to summarise the intervention effect on the primary and secondary outcomes with and without adjustment characteristics, referral to a treatment institution, and the interaction times.

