### Participants and sampling

Callers to the MedPAC Quitline and those who are actively recruited from schools and communities will be eligible service targets for the MedPAC Quitline. Youth who misuse drugs and have contacted the MedPAC Quitline will be eligible for inclusion in this proposed study if they (1) are 25 years of age or younger, (2) report having taken drugs within the past 30 days, (3) are able to communicate in Chinese, (4) agree to receive counselling via a messaging app (such as WhatsApp or WeChat), and (5) verbally consent to join the follow-up intervention. We will exclude potential subjects who have communication barriers and those who are undergoing other drug-misuse recovery treatments.

Because no previous study has conducted a brief telephone-based MI intervention, the sample size for the proposed RCT has been calculated according to a previous RCT that involved a computer-based MI intervention [18]. In this previous RCT, the mean number of drug-misuse consumptions per day decreased from 11.94 at baseline to 5.52 at 12 months for participants in the intervention group, and 9.22 at baseline to 8.61 at 12 months for those in the control group. The effect size was 0.64 for the MI intervention on drug-misuse reduction, with reference to the control group [18]. Based on these results, to detect a two-sided significant difference between groups with a power of 80 % and a significance level of 5 %, which are commonly accepted metrics for behavioural studies, the required sample size for this proposed RCT has been estimated to be 40 participants in each group. Given an expected retention rate of approximately 60 % at the 12-month follow-up, the target number of participants will be at least 134 (67 per group).

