### Measures

The demographics and baseline characteristics of participants will be collected during the baseline phone counselling. A structured questionnaire will be developed for this purpose by adopting or modifying international and/or locally validated instruments. The questionnaire will gather information on a participant’s (a) drug misuse profile, including the types of drugs used, his/her number of days of use, his/her daily drug consumption, and his/her history of quitting; (b) beliefs and values relating to drug use, using the Chinese Drug Involvement Scale [19]; (c) drug misuse-related knowledge [20]; (d) attitudes towards their drug abuse [20]; (e) contemplation stage of drug-misuse abstinence, using the Contemplation Ladder Tool [21]; (f) treatment needs and motivation, using the Texas Christian University Motivation and Readiness For Treatment form [22]; (g) self-efficacy to avoid drug use, using the Adolescent Relapse Coping Questionnaire [23]; (h) quality of life, using the EuroQol 5-Dimension 5-Level Questionnaire [24]; (i) depression level, using the Center for Epidemiologic Studies Depression Scale [25]; and (j) self-esteem, using the Rosenberg Self-Esteem Scale [26]. The Chinese versions of the above scales have been evaluated to show acceptable validity and reliability [19–26].

All participants will receive follow-up telephone calls from our trained research assistant at 1 week, 1 month, and 3, 6, 9, and 12 months. During each follow-up telephone call, the participants will be asked to complete the structured questionnaire (Table 1). Participants who are lost to one follow-up will be contacted again in the next follow-up.

**Table 1 Tab1:** Schedule of enrollment and follow-up assessments

Assessment	Time-point						
	Baseline	1 week	1 Month	3 Months	6 Months	9 months	12 Months
Informed consent for participants	×						
Eligibility screen for participants	×						
Telephone counselling	×						
Sociodemographic characteristics	×						
Randomization	×						
Intervention	× (twice per week)						
Self-reported drug misuse	×	×	×	×	×	×	×
Attempt to quit	×	×	×	×	×	×	×
Chinese drug involvement scale	×				×		×
Drug misuse-related knowledge	×				×		×
Attitudes towards the drug misuse	×				×		×
Contemplation ladder	×	×	×	×	×	×	×
TCU MOTForm	×			×	×	×	×
Adolescent relapse coping questionnaire	×			×	×	×	×
EQ-5D-5 L level	×				×		×
Center for Epidemiologic Studies Depression Scale	×				×		×
Rosenberg self-esteem scale	×				×		×

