### Outcomes

The primary outcome will be changes in the participants’ reductions in self-reported drug consumption at 12 months compared to that at baseline. Secondary outcomes will be (1) changes in the participants’ reductions in self-reported drug consumption at 6 months compared to that at baseline; (2) 30 days self-reported drug abstinence at 6 and 12 months; (3) changes in relapse risk among the quitters at 6 and 12 months compared to that at baseline; (4) changes in the participants’ contemplation stages at 6 and 12 months compared to those at baseline; and (5) treatment needs and motivation at 6 and 12 months compared to those at baseline.

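### The main analysis names odds ratios and risk differences for a primary outcome that is a quantitative change and was sized as a comparison of means

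*Protocol article*

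**What the plan says.** All references are to the protocol article.

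- **Outcomes:** "The primary outcome will be changes in the participants’ reductions in self-reported drug consumption at 12 months compared to that at baseline". No threshold or responder definition is attached. Of the five secondary outcomes, 30-day abstinence is the only one that is plainly binary.
- **Measures:** the drug-misuse profile covers "the types of drugs used, his/her number of days of use, his/her daily drug consumption", so consumption is collected as a quantity.
- **Participants and sampling:** the trial is sized from mean consumptions per day in an earlier trial. In its intervention arm "the mean number of drug-misuse consumptions per day decreased from 11.94 at baseline to 5.52 at 12 months for participants in the intervention group", against "9.22 at baseline to 8.61 at 12 months for those in the control group". The article adds: "The effect size was 0.64 for the MI intervention on drug-misuse reduction". From this it derives 40 per group for 80% power at two-sided 5%, raised to 67 per group (134 in total) for 60% retention.
- **Data analysis, descriptive paragraph:** group differences in sociodemographic factors and in outcomes are to be tested by chi-square if categorical and by analysis of variance if continuous.
- **Main analysis:** the effect measures listed are "Odds ratios, risk differences", with 95% limits. They apply to the primary outcome as well as the secondary ones, because the same sentence goes on to say that the "confidence intervals will be used to compare the primary and secondary outcomes between the two trial groups". Next, a GEE model is to summarise the effect on the same outcomes. Its distribution, link and effect measure are not stated.

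**The concern.** A risk difference needs a binary outcome, and an odds ratio needs a binary or ordinal one. Neither describes a change in amount consumed unless that change is first cut into categories. The Main analysis sentence nevertheless names the primary outcome explicitly, so it cannot be read as covering abstinence alone.

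The article thus gives instructions for the primary comparison that do not agree. One route leads to a difference in means, through analysis of variance or a GEE with identity link. The other leads to a responder comparison at a cut-point that the article does not give. Candidates such as any reduction, a 50% reduction or a median split could give different answers. If the choice is left until data are in hand, the primary result is open to selection, and the power statement would no longer describe the analysis performed.

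The outcome wording adds to the uncertainty. It speaks of a change in a reduction compared with baseline, but at baseline there is no reduction to change from.

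**Working it through.** **1. Which comparison was the trial sized for?**

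Inputs from Participants and sampling: effect size 0.64, two-sided 5%, power 80%, retention 60%.

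- Normal approximation: n = 2(1.960 + 0.842)² / 0.64² = 38.3, so 39 per group.
- Two-sample t-test: n = 39.3, so 40 per group, as stated. Power at 40 is 80.7%.
- Attrition: 40 / 0.60 = 66.7, so 67 per group and 134 in total, as stated.

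The plan's figures reproduce as a comparison of two means with 0.64 used as a standardised difference.

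**2. What would a dichotomy do to power? (illustration)**

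Assumptions that are not in the documents: normal change scores, a shift of 0.64 SD between arms, and a cut giving control response p_C. Then p_I = Φ(Φ⁻¹(p_C) + 0.64).

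Power = Φ[(d − 1.96·SE₀) / SE₁], where d = p_I − p_C, SE₀ = √(2p̄(1 − p̄)/n) and SE₁ = √([p_C(1 − p_C) + p_I(1 − p_I)]/n).

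Worked case: cut midway between the arms, n = 40.

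- p_C = 0.3745, p_I = 0.6255, d = 0.251, p̄ = 0.5.
- SE₀ = √(2 × 0.25 / 40) = 0.1118.
- SE₁ = √(2 × 0.3745 × 0.6255 / 40) = 0.1082.
- Power = Φ[(0.2510 − 0.2191) / 0.1082] = Φ(0.295) = 61.6%.

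| Analysis | Control vs intervention response | Power, 40 per arm | Power, 67 per arm | Evaluable per arm for 80% |
|---|---|---|---|---|
| Means (t-test) | – | 80.7% | 95.7% | 40 |
| Cut | 20% vs 42.0% | 56.9% | 79.3% | 69 |
| Cut | 30% vs 54.6% | 60.9% | 83.0% | 63 |
| Cut, midway | 37.5% vs 62.5% | 61.6% | 83.6% | 62 |
| Cut | 50% vs 73.9% | 59.8% | 82.0% | 64 |
| Cut, extreme | 10% vs 26.1% | 46.3% | 68.0% | 89 |
| Cut, extreme | 70% vs 87.8% | 49.6% | 71.8% | 82 |

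The 40-per-arm column uses the number that the plan expects to retain. The 67-per-arm column reflects the planned intention-to-treat analysis with last observation carried forward, and it assumes that the full 0.64 SD effect survives that imputation.

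Over the mid-range cuts (20% to 50%) the loss is 80.7 − 61.6 = 19 to 80.7 − 56.9 = 24 points at 40 per arm. At 67 per arm it is 95.7 − 83.6 = 12 to 95.7 − 79.3 = 16 points.

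**The case against.** The strongest reply is that the plan already contains a usable continuous analysis. The descriptive paragraph of Data analysis expressly includes outcomes when it assigns analysis of variance to continuous data. A GEE can be fitted to a quantitative outcome. The Abstract promises adjusted regression with baseline adjustment, and Study design states the comparison plainly as reduction in misuse at 12 months. On this view the sentence in Main analysis is a compressed list of measures for a mixed set of outcomes, and GEE family and link are details that an analysis plan would settle.

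Much of this stands. A reader might infer that the primary result cannot be produced at all without dichotomising. The documents do not support that, because a comparison of means is available in them. A reader might also infer that odds ratios belong to abstinence alone. That goes too far: contemplation stage could be analysed as ordinal, and the article does not say how relapse risk is scored.

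What does not fall away is the literal statement. Detail may be left to an analysis plan, but here the article positively names measures for the primary outcome that do not fit it. The continuous method stated elsewhere does not correct that sentence; it conflicts with it.

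**Conclusion.** The point holds as a misstated primary effect measure and a conflict between instructions. The primary outcome is quantitative, it is sized as a comparison of means, and it has no responder cut-off. Main analysis nevertheless assigns it odds ratios and risk differences. As written, either a mean difference or a responder comparison could be reported as the primary result, and the stated 80% power supports only the first.

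The power figures are conditional. It would be tempting to say that this plan loses about 20 points of power, but it states no dichotomy. The size depends on an assumed normal distribution, an assumed cut and the number analysed: roughly 19 to 24 points at 40 per arm and 12 to 16 points at 67 per arm for mid-range cuts, with lower power at extreme cuts. The contradiction does not depend on these figures. Because it decides which number is the primary result, it should be settled before any unblinded analysis.

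**What to change.** - **Main analysis, primary outcome:** state the effect measure as the between-arm difference in mean change in consumption from baseline to 12 months, with 95% CI, taken from the 12-month group effect in a GEE whose family and link match. Adjustment for baseline consumption is preferable and fits the Abstract's commitment to baseline adjustment. If skewed data are expected, a rate ratio from a log-link model could be prespecified instead.
- **Other outcomes:** use mean differences for the other quantitative scale outcomes. Restrict risk differences to binary outcomes such as 30-day abstinence, and odds ratios to binary or ordinal outcomes.
- **Descriptive paragraph:** make clear that the analysis of variance is not a second, competing primary analysis.
- **Outcomes and Abstract:** reword the primary outcome as the change in self-reported consumption from baseline to 12 months.

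The cost is wording only. Data collection and schedule do not change, and the 40 evaluable and 67 enrolled per group stand.

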**Methods:**

A two-group single-blind, randomised controlled trial will be conducted. Multiple approaches, including online and face-to-face methods, will be used to recruit the participants. The participants, aged 25 years or younger and reporting any drugs that they have taken within the past 30 days, will be recruited and randomised to receive either brief motivational interviewing via interactive instant-messaging (the intervention) or general health text-messages (comparator). The primary outcome will be the change in the participants’ reductions in self-reported drug consumption at 12 months compared to that at baseline. The secondary outcomes will be the changes in the drug-abusing participants’ reductions in self-reported drug consumption at 6 months, the changes in the drug-quitting participants’ 6- and 12-month contemplation stages and relapse risk compared to that at baseline, 30 days’ self-reported drug abstinence at 6 and 12 months, and the treatment needs and motivation at 6 and 12 months compared to that at baseline. The effectiveness of the proposed intervention will be examined with adjusted regression models, with adjustment for baseline characteristics and the use of an intention-to‐treat approach.

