### Resource and setting

This proposed study will be conducted in association with the Medical Peer Addiction Counselling Quitline Service (MedPAC Quitline), supported by the Beat Drugs Fund, Narcotics Division, Security Bureau of Hong Kong. The team of the School of Nursing at the University of Hong Kong established this first peer-oriented drug misuse quitline in 2020. Trained youth and young adult counsellors with a medical background provide peer-oriented drug-misuse counselling via MedPAC Quitline to drug-abusing youth and young adults and actively refer those in need to further treatment and rehabilitation services.

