### Randomisation and blinding

A simple complete randomisation method will be adopted. The subjects will be randomly allocated to either the intervention or the control group. The random numbers used for group assignment will be generated using a personal computer by another research assistant, who will not be involved in the subject recruitment. The randomisation will be performed by a research assistant who will open a serially numbered, opaque, sealed envelope that contains a card indicating the randomly allocated group. Because the subjects will be aware of their allocation according to the content received, we will be unable to completely blind them. However, a single-blind approach will be adopted, in which all outcome assessors and data analysts will be blinded to the group assignment.

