#### Intervention group

The interaction communication using brief MI will be applied via the chat function of IM apps (e.g., WhatsApp or WeChat). The intervention will be performed for 6 months at a frequency of at least twice a week. To begin the conversation, trained peer counsellors will actively contact the participants and explore their lifestyles and their current barriers to and facilitators of change. The counsellors will do this by asking participants about their current lifestyles, drug-misuse habits, and levels of stress to establish a collaborative relationship with and obtain a general understanding of each participant (opening strategy). To further understand why a participant does not intend to reduce his/her drug misuse, the counsellor (interventionist) will review a typical day of the subject (a typical day) and ask about the advantages and disadvantages of not reducing drug misuse. Each participant will receive further information about the health benefits of reducing or quitting drug use, if he/she is interested in doing so (providing information). To elicit information on discrepancies, each participant will be encouraged to talk about his/her ideal future and to compare the past and the present (the future and the present). The interventionist will also listen to, explore, and summarise the concerns of the participant (exploring concerns). The interventionist will resolve the ambivalence of the participant by describing what others have done in a similar situation and presenting options, while not urging a participant to make a decision (helping with decision*-making*). Importantly, the participant’s confidence about reducing or quitting his/her drug use will be enhanced throughout the process of receiving personalised health advice, as this advice will emphasise the health benefits of reducing or quitting and encourage the participant to be aware of resources that enable and facilitate such behavioural change. At the request of the participant, the interventionist will provide more comprehensive information and suggestions on how to reduce drug use, including the skills to overcome withdrawal symptoms.

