Referral need and results	×	×	×	×	×	×	×

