### Data analysis

Data analysis will be performed using the Statistics Package for the Social Sciences (SPSS) version 25.0 for Windows (SPSS Inc., Chicago, IL, USA). Analyses will be conducted on an intention-to-treat basis, with missing-value substitutions based on the last observation carried forward. A two-sided statistical significance level of 0.05 will be adopted for all analyses.

Descriptive statistics will be used to detail participants’ demographic characteristics and drug misuse profiles. Frequencies and percentages or means and standard deviations will be used to present categorical data and continuous data, respectively. The differences between intervention and control groups, in terms of sociodemographic factors and outcomes, will be compared using a chi-square test for categorical variables and by an analysis of variance for continuous variables.

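### The adjusted version of the main GEE includes variables that arise after randomisation, so it does not estimate the intention-to-treat effect, and neither version is named as primary

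*Protocol article*

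**What the plan says.** Under Main analysis, a GEE model "will be used to summarise the intervention effect on the primary and secondary outcomes". It is to be fitted "with and without adjustment characteristics, referral to a treatment institution, and the interaction times". The sentence does not limit the characteristics or the referral variable to baseline, does not define interaction times, and does not say which version carries the conclusion.

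Other parts of the protocol bear on this:

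- The Abstract announces adjusted regression models "with adjustment for baseline characteristics" and an intention-to-treat approach. The Data analysis section repeats the latter: "Analyses will be conducted on an intention-to-treat basis".
- On timing of the IM contact, the Intervention group section says: "The intervention will be performed for 6 months at a frequency of at least twice a week". Controls receive general health texts. The Discussion says participants may answer or stay silent as they choose.
- Under Resource and setting, the service's counsellors "actively refer those in need to further treatment and rehabilitation services". Both arms receive this basic service (Intervention section).
- The Table 1 row "Referral need and results" is ticked at baseline and at all six follow-ups to 12 months.

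**The concern.** A regression of outcome on arm recovers the randomised effect if the other covariates were fixed before allocation. Adding a variable that allocation can change creates two problems. If the variable carries part of the effect, holding it constant takes that part out of the arm coefficient. If an unmeasured trait such as motivation drives both the variable and the outcome, conditioning on it reopens the confounding that randomisation had closed.

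Interaction count, on the natural reading, is exposed to both problems. Because it is essentially zero in controls, the arm coefficient also becomes an extrapolation: treated participants with no interaction against controls. Referral may be exposed in the same way, because the protocol expects the intervention to raise help-seeking.

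What is at stake is the interpretation of the primary result. Two versions of the effect will exist, they may disagree, and no rule says which one answers the trial's question.

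**Working it through.** **1. The plan's own figure.** For an effect of 0.64 SD, two-sided 5% and 80% power, the normal approximation gives 2 × (1.960 + 0.842)² / 0.64² = 38.3, so 39 per arm. The t-test gives 39.3, so 40. With 60% retention, 40 / 0.60 = 66.7, so 67 per arm and 134 in total. The stated sample size reproduces, and this point does not change it.

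**2. Timing of each covariate.**

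| Covariate | When fixed | Related to arm? |
|---|---|---|
| Baseline characteristics | Before allocation | No, by randomisation |
| Interaction times, read as IM count | During the 6 months after allocation | Yes, by design: essentially zero in controls |
| Referral | Baseline and every follow-up to 12 months; the time-point used is not stated | Plausible, not stated |

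People already in other drug-misuse recovery treatment are excluded, so referrals that are acted on fall mainly after entry. A referral variable fixed strictly before randomisation would be harmless.

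**3. What the fully adjusted coefficient measures.** An illustrative simulation used a linear model with 40 analysed per arm and 3,000 runs per scenario. Positive values mean greater reduction in consumption. From the protocol: total effect 0.64 SD and 40 per arm. Assumed, not in the protocol:

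- about 30 replies on average in the intervention arm and none in controls;
- referral about 40% against 20%, with an effect of 0.3 SD;
- 0, 0.32 or 0.58 SD of the effect carried by interactions;
- unmeasured motivation that raises replies and referral and affects the outcome by 0 or 0.4 SD.

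Without a motivation effect, the coefficient should be 0.64 − 0.3 × (0.40 − 0.20) − (part through interactions) = 0.58 − (part through interactions). That is 0.58, 0.26 and 0.00, which the simulation matches.

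| Part through interactions (SD) | Motivation effect (SD) | Arm only | Arm + referral | Arm + referral + count |
|---|---|---|---|---|
| 0 | 0 | 0.64 | 0.59 | 0.58 |
| 0.32 | 0 | 0.64 | 0.57 | 0.25 |
| 0.58 | 0 | 0.64 | 0.55 | −0.01 |
| 0 | 0.4 | 0.64 | 0.52 | −0.07 |
| 0.32 | 0.4 | 0.63 | 0.52 | −0.39 |
| 0.58 | 0.4 | 0.63 | 0.51 | −0.64 |

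The arm-only model rejected the null in 71% to 80% of runs. The fully adjusted model did so in 33%, 10% and 6% in the first three rows. With no true effect but a motivation effect of 0.4 SD, the fully adjusted model averaged −0.63 and rejected in 41% of runs. The arm-only model and the model with referral only each rejected in about 5%.

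**4. Stronger assumptions for referral.** Take referral 40% against 15%, an effect of 0.8 SD, and motivation correlated 0.5 with the outcome. The part through referral is 0.25 × 0.8 = 0.20 SD, which leaves 0.44. Motivation confounding takes the referral-adjusted estimate down to about 0.35.

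Across the two sets of assumptions, adjusting for referral alone gives 0.35 to 0.59. The attenuation runs from (0.64 − 0.59) / 0.64 = 8% to (0.64 − 0.35) / 0.64 = 45%.

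**The case against.** The strongest reply is that the same sentence plans the model without these covariates, and the Data analysis section also compares outcomes between groups by chi-square test and analysis of variance. The randomised effect will therefore be available. This stands, and it limits the point to the adjusted version and to the missing choice between the two.

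A reader might infer more in four ways that the document does not support.

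- **That the post-randomisation model is the headline result.** The Abstract does say effectiveness will be examined with adjusted models, but it describes them as baseline-adjusted. That is a mismatch with Main analysis, not evidence that the contaminated model leads.
- **That referral is a consequence of the arm.** Both arms receive the basic service with referral, and referral is also recorded at baseline. A difference by arm is a fair inference from the aim of raising help-seeking, but it is not stated.
- **That the result will be reversed or the error rate inflated.** Those results depend on assumed inputs and on reading interaction times as an IM count. A group-by-time term is conceivable in a repeated-measures GEE, and under that reading they disappear.
- **That analyst blinding is broken.** The protocol says "all outcome assessors and data analysts will be blinded to the group assignment", and a count that is zero in one arm would reveal the arm. This again needs the count reading. Analyses within the intervention group are planned anyway, and blinding could still hold for the primary comparison. It is a secondary matter.

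**Conclusion.** The point holds in a limited form. The adjusted GEE, as worded, conditions on variables that arise after allocation. It therefore does not estimate the intention-to-treat effect and departs from the Abstract's baseline adjustment. The unadjusted GEE is sound in this respect, but nothing makes it, or a baseline-adjusted model, the primary analysis.

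For interaction times the conclusion rests on the natural reading as a count of IM exchanges. For referral it rests on the variable including follow-up values and on a plausible difference between arms. The simulations show that material bias is possible. They do not predict its size or direction, which cannot be fixed from the document.

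**What to change.** Reword the Main analysis sentence before any outcome data are analysed:

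- Name as primary, for the primary and secondary outcomes, a GEE with arm, time, arm-by-time and pre-randomisation covariates only: baseline consumption and a short pre-specified list of baseline characteristics. This also brings Main analysis into line with the Abstract.
- Remove post-randomisation referral and the IM interaction count from that model.
- Report referral by arm as an outcome.
- Use the interaction count only in a labelled exploratory compliance or mediation analysis. The Discussion already plans to look at level of participation.
- Define interaction times. If a group-by-time term was meant, keep it and call it that.

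The cost is a few lines of wording. No new data are needed, and the sample size stays at 134.
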